## Abstract

**Background and aim:**

Limitations of the currently recommended stepwise treatment pathway for type 2 diabetes mellitus (T2DM), especially the failure of monotherapies to maintain good glycemic control, have prompted use of early, more aggressive combination therapies.

The VISION study is designed to explore the efficacy and safety of vildagliptin as an add-on to metformin therapy compared with up-titration of metformin monotherapy in Chinese patients with T2DM.

**Methods:**

VISION, a 24-week, phase 4, prospective, randomized, multicenter, open-label, parallel-group study, will include 3312 Chinese T2DM patients aged ≥18 years who are inadequately controlled (6.5% >HbA1c ≤9%) by metformin (750–1000 mg/day). Eligible patients will be randomized to receive either vildagliptin plus metformin or up-titration of metformin monotherapy (5:1). Patients will also be subgrouped (1:1:1:1) based on their age and body mass index (BMI): <60 years and <24 kg/m^2^; <60 years and ≥24 kg/m^2^; ≥60 years and <24 kg/m^2^; and ≥60 years and ≥24 kg/m^2^.

**Conclusion:**

The VISION study will test the hypothesis that early use of combination therapy with vildagliptin and metformin will provide good glycemic control and will be better tolerated than up-titration of metformin monotherapy. The study will also correlate these benefits with age and BMI.

## Background

Type 2 diabetes mellitus, a chronic metabolic disorder of complex pathophysiology, is prevalent worldwide [1]. According to the 2011 estimates of the World Health Organization (WHO), there are currently approximately 346 million adults affected by diabetes globally [2]. In China, a total diabetes prevalence of 9.7% (92.4 million adults) was reported by the China National Diabetes and Metabolic Disorders Study in 2007–2008, while the prevalence of prediabetes was estimated to be 15.5% (148 million adults) [3]. The prevalence of diabetes was highest among individuals aged ≥60 years and among those with a body mass index (BMI) >30 kg/m^2^[3]. Management of diabetes aims at improving glycemic control, which is typically measured as reductions in glycated hemoglobin (HbA1c) [4]. Current guidelines define the target for glycemic control as HbA1c <7.0% or <6.5% [1,4]. Several classes of antihyperglycemic agents with different mechanisms of action are currently available. Metformin and the thiazolidinediones suppress insulin resistance while α-glucosidase inhibitors act within the gastrointestinal (GI) tract to lower postprandial glucose excursions. Sulfonylureas and meglitinides increase β cell insulin secretion in a glucose-independent manner. Dipeptidyl peptidase IV (DPP-IV) inhibitors and glucagon like peptide-1 (GLP-1) analogs improve insulin secretion and suppress glucagon secretion by glucose-dependent mechanisms [5].

Current clinical practice guidelines recommend a stepwise treatment pathway for diabetes [1]. Lifestyle modifications such as weight reduction, dietary adjustments, and physical exercise form the first step of treatment followed by initiation of monotherapy. Metformin is recommended as the first-line oral antihyperglycemic agent in most patients with T2DM by almost all clinical practice guidelines. Along with its favorable effect on blood glucose, metformin is associated with a low incidence of weight gain and hypoglycemia, and it also has cardioprotective properties [1,5-10]. Subsequent stepwise intensification of metformin monotherapy is recommended if glycemic control is inadequate [1,5,11]. In patients with persistent hyperglycemia even after the maximum effective and/or tolerated dose of metformin is used, the rapid addition of other antihyperglycemic agents is recommended [11]. If glucose control remains inadequate, another medication should be added to the initial therapy [1,11].

The stepwise treatment approach is, however, associated with several limitations. Lifestyle interventions are difficult to be implements and maintain, and have failed to achieve effective glycemic control alone [12]. Given the limitation of monotherapies to act on the multiple pathophysiological mechanisms involved in glucose control, they frequently fail to achieve the target glycemic goal [1]. Failure of monotherapies is also attributed to their inability to prevent deterioration of pancreatic β-cell function, which is commonly observed in diabetes [13,14]. Although monotherapies can provide initial glycemic control, several clinical studies have demonstrated failure of monotherapy to maintain long-term glycemic control [15]. The United Kingdom Prospective Diabetes Study (UKPDS 49), demonstrated that long-term monotherapy with either insulin, sulfonylureas, or metformin could not sustain the glycemic control initially achieved (HbA1c <7%). Approximately 50% and 75% of patients required the addition of at least one more pharmacological agent after 3 years and 9 years of follow-up, respectively [16]. A Diabetes Outcome Progression Trial (ADOPT) compared the durability of glycemic control in patients receiving rosiglitazone, metformin, or glyburide as initial monotherapy [17]. All these monotherapies eventually failed to sustain the targeted glycemic control over time. Furthermore, all were associated with high discontinuation rates, mainly due to drug-related adverse effects [17]. In another large observational study undertaken in the UK, approximately 50% of patients failed to achieve the target HbA1c level of <7% during the first year with sulfonylurea or metformin monotherapy. After 3 years of follow-up, neither of the monotherapies was able to maintain the target HbA1c in >70% patients who had initially achieved the goal during the first year [14]. Moreover, these agents were associated with several adverse events (AEs) such as hypoglycemia, weight gain, GI disturbances, peripheral edema, and potential cardiovascular effects [8].

As recommended in the traditional stepwise approach, intensification of therapy with higher doses has shown to be successful in improving glycemic control. However, the increased risk of AEs with dosage increases has resulted in impaired patient compliance and subsequently poor glycemic control [12]. For example, metformin therapy is associated with dose-dependent GI adverse effects such as diarrhea, flatulence, and abdominal discomfort, which often lead to treatment discontinuation [18,19]. In the UKPDS 33 study, intensive treatment with sulfonylureas or insulin was associated with an increased incidence of hypoglycemia and weight gain [20]. Moreover, the stepwise approach can also cause a delay in switching from monotherapy to combination therapy, which often leads to further deterioration of glycemic control [1,15,19].

Thus, limitations of the stepwise treatment approach and the progressive decline in pancreatic β-cell function in diabetes warrants new treatment strategies. Early use of more aggressive combination therapy, before responsiveness to monotherapy begins to decline, can be an effective approach [1,15]. This approach may provide several advantages, including greater glycemic control and the ability to act on different pathological mechanisms involved in glucose dysregulation [1]. Additionally, early interventions are particularly beneficial as they can slow the onset and progression of T2DM and its associated complications [1]. Combination therapy typically requires lower doses than those required for individual monotherapies, which can reduce the adverse effects associated with higher doses of monotherapy and thus improve tolerability [15]. The EMPIRE study demonstrated that early use of combination therapy comprising submaximal doses of antihyperglycemic agents can improve glycemic control without significantly increasing the occurrence of adverse effects. The use of rosiglitazone, a thiazolidinedione, as add-on therapy with submaximal doses of metformin was shown to be non-inferior to up-titration of metformin to its maximal effective dose in reducing HbA1c [19]. Furthermore, add-on therapy was better tolerated than metformin alone, with a lower incidence of GI AEs [19]. However, the potential cardiovascular effects associated with rosiglitazone has limited the clinical use of this combination therapy [1]. Thiazolidinediones are also associated with weight gain and thus the benefits of their combination with metformin should be weighed against the potential risk. Similarly, use of traditional combinations such as metformin with sulfonylureas, or metformin with insulin has limited clinical use owing to the associated hypoglycemia and weight gain [1,19,21]. Thus, the critical question that still remains to be answered is: which antihyperglycemic agents can be used effectively at early stages in the treatment of T2DM to effectively complement metformin? [13,21].

The multiple physiological actions of the incretin hormone glucagon-like peptide-1 (GLP-1), which include sensitization of β cells, augmentation of glucose-stimulated insulin secretion, inhibition of glucagon secretion, delayed gastric emptying, and stimulation of insulin biosynthesis make it a potentially useful therapeutic agent for the treatment of diabetes [22]. However, as GLP-1 is rapidly degraded by DPP-IV enzyme, which limits its effects, the use of DPP-IV inhibitors to prolong the half-life of the circulating endogenous peptide has proved an effective approach to developing new therapeutic antidiabetic agents [22]. Recent reviews of randomized studies of a minimum of 12 weeks’ duration have suggested that DPP-IV inhibitors are well tolerated, with no reports of severe hypoglycemia and weight gain in patients with T2DM [23,24].

Vildagliptin, a potent, selective, and orally active second-generation DPP-IV inhibitor, was recently approved for the treatment of T2DM. Vildagliptin has been shown to reduce fasting plasma glucose (FPG) and postprandial plasma glucose (PPG) levels and 24-hour glycemic excursions, and suppress postprandial plasma glucagon levels by inhibiting the activity of DPP-IV enzyme to raise the levels of fasting and postprandial active incretins [25-28]. It also improves insulin sensitivity, augments meal/postprandial plasma insulin levels, and enhances both α- and β-cell functions [28-31]. Improvements in functioning of the islets of Langerhans in individuals with well-controlled T2DM receiving vildagliptin under fasting conditions suggest a role beyond the enhancement of meal-induced GLP-1 and glucose-dependent insulinotropic polypeptide (GIP) activity [32]. In drug-naïve patients with mild hyperglycemia, vildagliptin reduced the progressive deterioration of glycemic control over 2 years. This indicates a favorable effect in preventing the deterioration of β-cell function [33]. In clinical studies, vildagliptin has been shown to improve glycemic control when administered as monotherapy or combination therapy in drug-naïve patients and in treatment-experienced patients [13,25]. In drug-naïve patients with T2DM, significant and progressive reductions in HbA1c were seen over 12 weeks of vildagliptin monotherapy (100 mg) [34].

The use of vildagliptin in combination with metformin has been reported to be well tolerated, with no reports of weight gain or severe hypoglycemia [35]. In patients poorly controlled with insulin monotherapy, the effectiveness of add-on vildagliptin therapy was investigated in a 24-week, double-blind, randomized clinical trial. The addition of vildagliptin not only improved glycemic control but also reduced the severe hypoglycemic events associated with insulin monotherapy [36]. Moreover, vildagliptin has also been found to have a weight-neutral effect, both as monotherapy and as combination therapy in patients with T2DM [25].

These reports have raised an important question – will a combination of vildagliptin plus metformin be both effective in achieving glucose control and well tolerated? The multiple mechanisms of action of vildagliptin in regulating glucose levels can complement the action of metformin, which lowers plasma glucose without affecting insulin secretion. Vildagliptin exerts its glucose-lowering effect through an increase in glucose-dependent insulin secretion, improving the sensitivity of both α and β cells to glucose, as well as suppressing FPG, PPG and postprandial glucagon secretion [13,25,26,37]. Several studies have demonstrated the superior efficacy of vildagliptin/metformin combination therapy in achieving target glycemic goals in comparison with metformin monotherapy [9,13,21,34]. The combination regimen was also safer, with no increased risk of hypoglycemia, weight gain or cardiovascular events [13]. Long-term vildagliptin/metformin combination therapy has also been shown to have beneficial effects on β-cell function [26]. Taken together these findings provide a rationale for the clinical use of vildagliptin plus metformin in patients with T2DM.

The VISION study ‒ VIldagliptin 50 mg bid as an add-on to metformin 500 mg bid compared with metformin up to 1000 mg bid in Chinese patients with type 2 diabeteS Inadequately controlled on metformin 500 mg bid mONotherapy ‒ was designed to explore differences in the efficacy and safety of vildagliptin as add-on therapy to metformin compared with up-titration of metformin in patients with T2DM inadequately controlled on metformin monotherapy. This study will therefore address the question as to whether the combination of submaximal metformin and vildagliptin will provide equivalent glucose control and less AEs compared with metformin up-titration. It also aims to evaluate if the beneficial effects of vildagliptin/metformin combination therapy can be correlated with various factors such as obesity and patient age. The efficacy and safety results of the VISION study will be published in due course after its completion.

## Materials and methods

### Subjects

Male and female Chinese T2DM patients (WHO/IDF criteria [38]) aged >18 years with HbA1c levels ranging between 6.5% and 9.0% and BMI between 22 and 45 kg/m^2^ at visit 1 who have received metformin at a stable dose of 750–1000 mg daily for at least 12 weeks before screening will be enrolled in the study. The patients will be required to maintain their individual eating and exercise habits during the study, and to follow all the study requirements. Written informed consent will be obtained from each patient prior to enrollment. Exclusion criteria for the study are listed in Table 1.

**Table 1 T1:** Exclusion criteria for the VISION study

	
**1.**	Pregnant or lactating women
**2.**	Medical history of following diseases:
	• Type 1 diabetes mellitus or diabetes caused by pancreatic injury or secondary diabetes: Cushing syndrome or acromegaly
	• Acute complications of diabetes: ketoacidosis or non-ketotic hyperosmolar coma within the past 3 months
	• Acute infections within 4 weeks prior to the screening (visit 1) that may affect the efficacy and safety of the study
	• Any obvious diabetic complications such as symptomatic autonomic neuropathy, gastroparesis, worsening hyperglycemia in the absence of any comorbid illnesses, and conditions that may affect blood glucose
	• History of kidney disease or clinical diagnosis of renal insufficiency indicated by serum creatinine ≥132 μmol/L (≥1.5 mg/dL) in males, and ≥123 μmol/L (≥1.4 mg/dL) in females
	• History of a liver disease such as cirrhosis, hepatitis B, or hepatitis C (except carriers) or Alanine transaminase (ALT), aspartate aminotransferase (AST) greater than 2 times the ULN or total bilirubin greater than 2 times the ULN
	• History of acute and chronic pancreatitis
	• Malignant tumor in the past 5 years, including leukemia and lymphoma (except for carcinoma in situ of the skin)
	• Torsades de pointes ventricular tachycardia or persistent, clinically relevant ventricular tachycardia or ventricular fibrillation or second-degree atrioventricular block (Mobitz type I and II) or third-degree atrioventricular block, or QTc prolongation (>500 ms)
	• Myocardial infarction, coronary artery bypass surgery or percutaneous coronary intervention, unstable angina, or stroke within the past 6 months
	• Congestive heart failure requiring medical treatment
**3.**	Fasting plasma glucose >15 mmol/L (>270 mg/dL) at visit 1
**4.**	Clinically significant thyroid-stimulating hormone levels outside the normal range at visit 1
**5.**	Use of concomitant medications:
	• Other antihyperglycemic agents besides metformin within 12 weeks of visit 1
	• Long-term glucocorticoids (>7 consecutive days of treatment) within 4 weeks of visit 1
	• Treatment with growth hormone or similar drugs
	• Treatment with class Ia, Ib, or Ic, or class III antiarrhythmics
	• Treatment with any drug with known and frequent toxicity to a major organ system within the past 3 months
**6.**	Use of other investigational drugs at visit 1, or within 30 days or 5 half-lives of visit 1, whichever is longer
**7.**	History of active substance abuse (including alcohol) within the past 2 years
**8.**	Potentially unreliable patients or patients who, in the opinion of the investigator, are unsuitable for the study

ULN: upper limit of normal.

### Study design

The VISION study is a 24-week prospective, randomized, multicenter, open-label, parallel-group controlled study. The planned study design is represented in Figure 1.

**Figure 1 F1:**
[figure not shown]
Design of the VISION study.

Patients participating in the study will be subgrouped (1:1:1:1) based on their BMI and age into 4 groups: (1) <60 years and BMI <24 kg/m^2^; (2) <60 years of age and BMI ≥24 kg/m^2^; (3) ≥60 years of age and BMI <24 kg/m^2^; and (4) ≥60 years of age and BMI ≥24 kg/m^2^. In each group, patients will be randomized according to the study design. At visit 1, patients meeting the inclusion criteria will be assigned to open-label metformin 500 mg bid for a 4-week lead-in period. At visit 2, patients will be randomized in a ratio of 5:1 to receive either vildagliptin 50 mg bid plus metformin 500 mg bid (Group A) or metformin 500 mg tid (Group B) for the next 4 weeks. From visit 3 to the end of the study, Group A patients will continue to receive the maintenance dose of vildagliptin 50 mg bid plus metformin 500 mg bid, while group B patients will receive metformin 1000 mg bid.

The primary, secondary, and exploratory objectives of the study are shown in Table 2. The study drug will be discontinued if it shows unsatisfactory efficacy at week 12 (i.e., FPG >13.3 mmol/L [240 mg/dL]) confirmed by a repeated measurement in the absence of any concurrent illness. Worsening of glucose levels in the absence of any other explainable concurrent disease or emergency condition that can affect glucose levels, the occurrence of AEs including GI side effects or clinically significant changes in laboratory parameters, or an abnormality that, in the opinion of the investigators, requires immediate withdrawal of treatment, will also lead to the study drug being discontinued. An inexplicable increase in levels of liver enzymes (aspartate transaminase, alanine aminotransferase and total bilirubin) without any clinical signs that is confirmed by a repeat measurement within 3 working days, pregnancy, severe or frequent hypoglycemia (i.e., unexplained hypoglycemic events requiring the assistance of another person or >3 hypoglycemic events within a week), treatment with prohibited concomitant medications, or any other deviation from the treatment protocol will also lead to treatment discontinuation. The reason for a patient discontinuing treatment will be recorded in the case report form.

**Table 2 T2:** Primary, secondary, and exploratory objectives of the VISION study

	
**1.**	**Primary objective:**
	• To demonstrate that the change from baseline in HbA1c levels after 24 weeks of treatment with vildagliptin 50 mg bid as add-on therapy to metformin 500 mg bid is non-inferior to high-dose metformin
**2.**	**Secondary objectives:**
	• To demonstrate in predefined patient subgroups [based on body mass index (BMI <24 and ≥24 kg/m^2^) and age (<60 and ≥60 years)] that vildagliptin add-on therapy to metformin is non-inferior to high-dose metformin in the change from baseline in HbA1c levels
	• To determine the percentages of patients achieving the target HbA1c level of ≤6.5% in the two treatment arms of the overall population and in the predefined subgroups
	• To determine the percentages of patients achieving the target HbA1c level of ≤6.5% in the two treatment arms of the overall population and in the predefined subgroups
	• To determine the mean change from baseline to 24 weeks in fasting plasma glucose in the overall population and in the predefined subgroups
	• To determine the mean change from baseline to 24 weeks in 2-hour postprandial glucose in a subsample of 464 patients with type 2 diabetes mellitus
	• Safety analysis
**3.**	**Exploratory objectives:**
	• To determine the mean change from baseline to 24 weeks in body weight and lipid parameters in the overall population and in the predefined subgroups
	• To determine the change from baseline to 24 weeks in β-cell function in a subsample of 464 patients with type 2 diabetes mellitus

BMI: body mass index; HbA1c: glycated hemoglobin.

Treatment will also be discontinued if the patient cannot tolerate the GI symptoms associated with a dose increase at visit 2. If patients in Group B cannot tolerate the GI symptoms at visit 3, the dose of metformin can be decreased by one tablet (250 mg) until the GI symptoms improve. After that, the dose will be gradually increased over 1–2 weeks. The dose of the metformin in Group B will be at least 500 mg bid until week 12. After week 12 (visit 4), dose adjustments of metformin will not be allowed at any time. Adjustment of the vildagliptin dose will not be allowed throughout the study.

Patients discontinuing the study drug, including those who do not attend the last visit, will be assessed for safety within 30 days of receiving their last dose. If all randomized patients complete the 24-week, open treatment period, the study will be considered completed. Premature termination of the study will be notified to the institutional review boards and/or ethics committees.

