### Data analysis

Intention-to-treat (ITT) analysis will be performed. The full analysis set (FAS) will include all randomized patients who took the study drugs at least once and had at least 1 primary or secondary efficacy evaluation after baseline. For assessment of missing primary efficacy variables, the last observation carried forward (LOCF) technique will be used. The per-protocol set (PPS) will include ITT patients completing at least 22 weeks of treatment, and those who discontinued the study due to a poor therapeutic response (FPG >13.3 mmol/L [240 mg/dL]) after 12 weeks of treatment, provided they have no major protocol deviations and had a valid assessment of HbA1c levels within 7 days after their last dose of study drug. Any major deviation from the protocol will be identified and documented in the analysis plan. Patients will be analyzed in the treatment group to which they were randomly assigned for the efficacy assessment.

The safety analysis set (SAS) will include patients who took the study drugs at least once and had at least 1 safety assessment after baseline. The safety analyses will be according to the patients’ treatment, and will include the description of any AEs.

The FAS set will be used as the primary population for the primary efficacy variable, the change from baseline in HbA1c levels at 24 weeks. The primary efficacy variable will be analyzed using an analysis of covariance (ANCOVA) model and the LOCF approach.

Non-inferiority of the study drug will be analyzed using the null hypothesis and a unilateral alternative hypothesis, which are defined as follows:

$$H_{0},\delta_{\mathrm{vildagliptin}}\geq \delta_{\mathrm{metformin}}+0.3\%$$

$$H_{a},\delta_{\mathrm{vildagliptin}}<\delta_{\mathrm{metformin}}+0.3\%$$

where δ represents the change from baseline.

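### The primary objective names high-dose metformin as comparator, but the dosing rules let individual Group B patients stay on a reduced dose from week 12 to week 24 and still be analysed as that comparator

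*Protocol article*

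**What the plan says.** All dosing statements are in the Study design section of the protocol article, including the text after Table 2.

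- **Planned dose.** Everyone takes metformin 500 mg bid in the lead-in. Group B takes 500 mg tid for four weeks. From visit 3 to the end of the study Group A stays on vildagliptin plus metformin 500 mg bid, "while group B patients will receive metformin 1000 mg bid".
- **Intolerance at the first increase.** "Treatment will also be discontinued if the patient cannot tolerate the GI symptoms associated with a dose increase at visit 2".
- **Intolerance at visit 3, Group B only.** Here "the dose of metformin can be decreased by one tablet (250 mg) until the GI symptoms improve". The next sentence reads "After that, the dose will be gradually increased over 1–2 weeks".
- **Floor.** "The dose of the metformin in Group B will be at least 500 mg bid until week 12".
- **Freeze.** "After week 12 (visit 4), dose adjustments of metformin will not be allowed at any time".

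The primary objective in Table 2 is to show that vildagliptin "as add-on therapy to metformin 500 mg bid is non-inferior to high-dose metformin". The subgroup objective uses the same comparator label. Elsewhere the article describes the comparator as titration: the expanded study title at the end of the Background gives metformin up to 1000 mg bid, and the Abstract and Conclusion speak of up-titration or upward titration.

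Under Data analysis, the FAS requires one dose and one post-baseline efficacy evaluation, and efficacy is analysed as randomized. For the other set, "The per-protocol set (PPS) will include ITT patients completing at least 22 weeks of treatment", subject to there being no major protocol deviations, which are to be documented in the analysis plan. Neither definition mentions the metformin dose reached.

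**The concern.** The floor is the dose the patient took in the lead-in and the metformin dose Group A takes throughout. A Group B patient at or near the floor at visit 4 has, for the 12 weeks leading to the primary HbA1c measurement, a treatment that is not what the primary objective names. The dose cannot be raised after that point.

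In a non-inferiority trial a weakened control makes success easier. If a noticeable share of Group B is below the planned dose, a positive result supports non-inferiority to metformin titrated as tolerated. It does not by itself support non-inferiority to high-dose metformin. The trial is also open-label, and the article describes metformin reduction for Group B alone.

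**Working it through.** **1. The dose statements side by side**

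| Statement | Group B dose, visit 3 to week 24 |
|---|---|
| Planned schedule | 1000 mg bid (2000 mg/day) throughout |
| GI intolerance at visit 3 | one 250 mg tablet less (1750 mg/day), then re-increase |
| Stated floor until week 12 | 500 mg bid (1000 mg/day) |
| After week 12 | no adjustment |

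Going from 2000 to 1000 mg/day takes (2000 − 1000)/250 = 4 tablets. A single one-tablet reduction never reaches the floor, so the floor matters only if larger or repeated reductions are allowed. The text does not say whether they are. Nor does it say what dose the re-increase must reach, or by when.

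**2. The plan's own figure, to fix the precision**

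Inputs: SD 1, true difference 0, one-sided 0.05, 90% power (Sample size estimations); 5:1 allocation (Study design); margin 0.3 (hypotheses under Data analysis).

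n(B) = (1.645 + 1.282)² × 1² × (1 + 1/5) / 0.3² = 114.2, rounded up to 115. Total = 6 × 115 = 690, which is the stated number per subgroup.

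The margin of 0.5 printed in the sample size section gives 252 instead. That discrepancy is a separate matter; 0.3 is used here.

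Overall, with four subgroups: 4 × 115 = 460 in Group B and 4 × 575 = 2300 in Group A.

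SE = √(1/460 + 1/2300) = 0.0511.

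**3. Effect of under-titration**

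Let f be the share of Group B at the floor, and D the HbA1c benefit of full up-titration over 500 mg bid. The documents give neither, so both are assumptions. The control effect shrinks by f × D. If Group A is truly 0.3 points worse than full-dose metformin, the chance of declaring non-inferiority is Φ(f × D/SE − 1.645).

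For f = 10% and D = 0.3: 0.03/0.0511 = 0.587, and Φ(−1.058) = 14.5%.

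| f at the floor | D = 0.2 | D = 0.3 | D = 0.5 |
|---|---|---|---|
| 0% | 5.0% | 5.0% | 5.0% |
| 5% | 7.4% | 8.8% | 12.4% |
| 10% | 10.5% | 14.5% | 25.3% |
| 20% | 19.4% | 31.9% | 62.3% |

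**4. If affected patients are only one tablet down**

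Assume a linear dose response. One tablet is 250/1000 = one quarter of the distance to the floor, so the loss per patient is D/4. With D = 0.3:

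- f = 10%: 0.10 × 0.075 = 0.0075; 0.0075/0.0511 = 0.147; Φ(−1.498) = about 6.7%.
- f = 20%: 0.20 × 0.075 = 0.015; 0.015/0.0511 = 0.294; Φ(−1.351) = about 8.8%.

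**5. One subgroup**

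SE = √(1/115 + 1/575) = 0.102. With D = 0.3 and f = 10% at the floor, the rate is 8.8%, before any Hochberg adjustment.

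**The case against.** The strongest reply is that this is a boundary case. The allowance covers only individual Group B patients with GI intolerance at visit 3. The stated step is one tablet, and the next sentence calls for the dose to go up again. Patients who could not tolerate the first increase have already been discontinued, so those reaching visit 3 have had four weeks on 500 mg tid. GI side effects can also lead to discontinuation later. Resting at 500 mg bid until week 24 is permitted but is not the planned path. Titration to tolerance is also a legitimate comparator, and against that comparator the error rate stays at 5%.

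Most of this stands, and it rules out three stronger readings that a reader might infer:

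- **That the control arm as a whole may be held at its lead-in dose.** The documents plan 1000 mg bid for every Group B patient and allow exceptions for individuals.
- **That neither analysis compares Group A with up-titrated metformin.** Both do, for every Group B patient who reaches and keeps the planned dose. What is missing is a guarantee that this holds for all of them.
- **That reduced-dose patients are certain to be in the PPS.** Nothing shown excludes them, and on this text a permitted reduction is not a deviation. But major deviations are left to an analysis plan that is not shown.

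The objection does not remove the mismatch in labels. Table 2 does not say titration to tolerance, and the planned schedule and the reduction rule describe different treatments after visit 3. The FAS, which is the primary population, has no dose criterion.

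**Conclusion.** The point holds as a mismatch between the comparator named in the primary and subgroup objectives and the one the dosing rules can deliver. A Group B patient on a reduced dose at visit 4 keeps it to week 24 and counts in the primary analysis as high-dose metformin. The direction is clear as long as a higher metformin dose lowers HbA1c more: any such under-titration favours non-inferiority.

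The size cannot be read from the documents. The illustrative rise from 5% to about 14.5% assumes 10% of Group B at the floor, a 0.3-point benefit of up-titration, SD 1, and 2760 evaluable patients at 5:1. It falls to about 6.7% if those patients are one tablet down and the dose response is linear. The larger entries in the table show sensitivity to the assumptions and are not evidence about this trial. The inflation also exists only if the claim is about full-dose metformin. Worded as titration to tolerance, the claim carries no such error.

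**What to change.** 1. **Reconcile the dose statements.** The planned schedule for Group B from visit 3 and the reduction, floor and freeze rules after Table 2 should describe one treatment, including how far a reduction may go and what the re-increase aims at and by when. Which rule is right is for the sponsor; none is proposed here.
2. **Align the wording.** As the rules now stand, the primary and subgroup objectives and the conclusion should refer to metformin up-titrated as tolerated up to 1000 mg bid, which fits the study title in the Background.
3. **Report the dose delivered.** Give the distribution of Group B metformin dose at visits 4 and 5 beside the primary result, so that readers can judge the dilution.
4. **Keep any dose-restricted analysis supportive.** An analysis limited to Group B patients at the planned dose may be run as a labelled sensitivity analysis. It should be neither a PPS criterion nor a condition for the claim, because it selects on post-randomisation tolerance in one arm and so breaks the randomized comparison.

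The cost is wording and one table. Table 3 already schedules metformin dosage records at every visit, so no new data are needed.
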